#### Data management

Study data will be managed by the trial coordinator and research fellow under the supervision of the chief investigator and the study statistician.

Data stored on hospital computers will be password protected and in locked rooms in the local hospital radiotherapy and/or radiology (imaging data) departments, only accessible by the local research team. Each patient is assigned a unique patient study ID number at enrolment (based on site and trial number allocated during randomisation step), which will be used on all trial documentation. This pseudoanonymisation step will prevent the patient from being identified by those outside the local research team. The local investigator will keep a subject enrolment and identification log that contains the key to the code, that is, a record of the personal identification data linked to each patient study ID number.

In compliance with Good Clinical Practice guidelines and in accordance with the University of Leeds Code of Conduct and Research Ethics, the chief or local principal investigator will maintain all records regarding the conduct of the RO-PIP study. These will be securely archived for up to 20 years if required.

#### Statistical analysis

As this is a feasibility study, it will not involve hypothesis testing to identify whether the intervention has had an impact. Instead, data analysis will be descriptive and involve summary statistics. The analysis of all primary endpoint and all secondary endpoints relating to recruitment and withdrawals from the trial will take place at the end of the 24-month recruitment period. Final analysis of all other endpoint data will be carried out 6 months after the final participant has been randomised.

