### Study setting

The planned study is a prospective two arm (HDR-BT and SBRT) randomised (1:1) feasibility trial aiming to recruit a total of 60 patients with locally recurrent prostate cancer across three tertiary referral oncology sites (Christie Hospital NHS Foundation Trust, Leeds Teaching Hospitals NHS Trust and Mount Vernon Cancer Centre, UK). The study will open for recruitment in September 2022, and the estimated primary recruitment completion date is in September 2024 and study completion date in September 2026.

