#### PROMs assessment

Changes in patient-reported health-related quality of life (QoL)/PROMs will be assessed using the following validated questionnaires: Expanded Prostate Cancer Index Composite-26 (EPIC-26) (prostate cancer-related QoL and functional outcomes), European Organization for the Research and Treatment of Cancer Quality of Life Questionnaire (EORTC QLQ)-C30 (general QoL Score) and IPSS (urinary and sexual functional outcomes). The specific time points for these evaluations are:

Baseline assessment (prior to salvage treatment).1 month post-treatment completion.3 months post-treatment completion.6 months post-treatment completion.12 months post-treatment completion.24 months post-treatment completion.

The PROMs and quality-of-life assessments will not require a separate face-to-face meeting as these will be posted out to the participants. Follow-up after 2 years will be according to local policy.

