### Outcomes

#### Primary outcome

Recruitment rates for the whole 24-month recruitment period will be reported overall and per recruiting site. The average recruitment rate per month and in total over the formal monitoring period will be reported.

The study recruitment period is 24 months. To show that patient recruitment targets for a phase III RCT can be met within an adequate timeframe, a ‘steady state’ of recruitment should be observed. In this feasibility study, formal monitoring of recruitment will begin from the start of the patient recruitment where an average of two patients per month must be randomised over the remaining recruitment period in order to demonstrate a ‘steady state’ of recruitment.

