#### Secondary outcomes

Incidence of patient-reported acute (0–3 months) and long-term toxicity (>3 months) and impact on QoL determined by EPIC-26 (prostate cancer related QoL and functional outcomes), EORTC QLQ-C30 (general QoL score) and IPSS (urinary and sexual functional outcomes) measurements (key secondary endpoint).Incidence of clinician-reported treatment toxicity as per CTCAE V.5.0.Other feasibility endpoints include screening log summaries, treatment and questionnaire compliance, withdrawal rate and reasons for non-recruitment.

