#### Exploratory outcomes

MRI biomarkers at 1 month and 1 year post-treatment predictive of toxicity based on PROMs.Hypoxia levels based on a hypoxia associated gene signature obtained from the presalvage RT biopsy correlated with MRI biomarkers.Changes in the levels of inflammatory cytokine signatures from urine and blood obtained at baseline and after reirradiation in relation to PROMs.Multiple measures of image quality and reproducibility of prostate functional imaging (eg, diffusion coefficient values from IVIM sequences) for measuring tumour biology will be summarised.

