### Recruitment

Overall, 60 patients will be recruited over a 24-month period, approximately 2–3 patients per month (across 3 sites).

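### The final analysis of toxicity, PROM and MRI data is fixed at 6 months after the last randomisation, before most 24-month and, under steady accrual, at least a quarter of 12-month assessments are due

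*Protocol article*

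**What the plan says.** All references are to the protocol article.

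- **Statistical analysis** sets two dates. The primary endpoint and "all secondary endpoints relating to recruitment and withdrawals from the trial will take place at the end of the 24-month recruitment period". For everything else, "Final analysis of all other endpoint data will be carried out 6 months after the final participant has been randomised".
- **Secondary outcomes** names the key secondary endpoint: "Incidence of patient-reported acute (0–3 months) and long-term toxicity (>3 months"), together with impact on quality of life.
- **PROMs assessment** schedules questionnaires at baseline and 1, 3, 6 and 12 months after treatment, the last at "24 months post-treatment completion".
- **Table 1** carries clinician-reported adverse events and PSA through 12, 18 and 24 months, and MRI to 12 months.
- **Exploratory outcomes** includes "MRI biomarkers at 1 month and 1 year post-treatment predictive of toxicity based on PROMs".
- **Study setting** opens recruitment in September 2022; "the estimated primary recruitment completion date is in September 2024 and study completion date in September 2026".
- **Sample size** justifies 30 patients per arm as enough to estimate toxicity rates for the key secondary endpoint in each arm, and says these rates, with the recruitment information, will determine whether a larger trial is feasible.

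**The concern.** The analysis date does not fit the follow-up schedule. A final analysis 6 months after the last randomisation cannot contain the 12-, 18- or 24-month assessments of patients recruited late, although the study stays open for a further 18 months to collect them.

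The clocks also differ. The analysis is timed from randomisation, whereas PROMs and MRI are timed from the end of treatment. With any gap between the two, the last patients have not reached even their 6-month questionnaire, which is the first scheduled PROM beyond 3 months and so the first that informs long-term toxicity.

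At stake are the completeness and precision of the late toxicity rates that the trial is sized to estimate and that feed into the decision on the next trial. Withdrawal is analysed earlier still, at month 24, when patients have been on study for very different lengths of time.

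**Working it through.** **Inputs**

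- 60 patients over 24 months (Recruitment): "Overall, 60 patients will be recruited over a 24-month period, approximately 2–3 patients per month (across 3 sites").
- Steady accrual from the start (Primary outcome): "formal monitoring of recruitment will begin from the start of the patient recruitment where an average of two patients per month must be randomised". This supports uniform accrual as the base case.
- Final analysis at month 24 + 6 = 30 from first recruitment, about March 2025. Study completion, September 2026, is month 48.
- Lag d from randomisation to treatment completion: not stated. Either treatment takes about 2 weeks at most (Interventions). I assume d = 0 to 2 months, with 3 months as a sensitivity value.

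**Plan's own figure.** 60 / 24 = 2.5 per month, which agrees with the stated 2–3 per month.

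**Patients who have reached visit v by month 30**

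Number = 2.5 × min(24, 30 − v − d)

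| Visit | d = 0 | d = 1 | d = 2 | Not yet due, d = 0 to 2 |
|---|---|---|---|---|
| 6 months | 60 | 57.5 | 55 | 0–8.3% |
| 12 months | 45 | 42.5 | 40 | 25–33.3% |
| 18 months | 30 | 27.5 | 25 | 50–58.3% |
| 24 months | 15 | 12.5 | 10 | 75–83.3% |

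Example: 24 months with d = 2 gives 2.5 × (30 − 24 − 2) = 10. Per arm, 24-month data exist for 10/2 = 5 to 15/2 = 7.5 patients. With d = 3 the 12- and 24-month counts fall to 37.5 and 7.5.

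PROMs have no 18-month visit, so that row concerns adverse events and PSA only. Table 1 gives no anchor for those follow-up times; if they count from randomisation, the d = 0 column applies.

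**Sensitivity to accrual shape** (d = 0 to 3). With t = min(24, 30 − v − d)/24, the share reached is t² for linearly rising accrual and 1 − (1 − t)² for linearly falling accrual.

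- Rising: 44–61% of 12-month and 94–98% of 24-month visits not yet due.
- Falling: 6–14% of 12-month and 56–77% of 24-month visits not yet due.

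**Precision**

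- Zero events in n patients: exact upper 95% limit = 1 − 0.025^(1/n). For n = 30 this is 11.6%; n = 27, about 13%; n = 22 and n = 20 (12 months), 15% and 17%; n = 7 (24 months), 41%.
- Assumed toxicity rate of 20%: half-width = 1.96 × √(0.2 × 0.8 / n), which is 14.3 percentage points for n = 30, 16.5 for n = 22.5 and 28.6 for n = 7.5.

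**Withdrawal at month 24.** Uniform entry gives a mean time on study of 24/2 = 12 months. As an illustration only, assume 20% withdraw by 24 months at constant hazard: λ × 24 = −ln(0.8) = 0.223. The expected crude proportion over all 60 is 1 − (1 − 0.8)/0.223, about 10%.

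**Study completion date.** At month 48 all 12- and 18-month visits are due. Counted from treatment completion, 2.5 × d = 0 to 5 patients would have their 24-month visit after September 2026.

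**The case against.** The strongest reply is that the timing does less harm than it seems.

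- **The primary endpoint is untouched.** Recruitment is analysed at month 24, the analysis is descriptive, and no test or power figure is affected. This stands.
- **The key secondary endpoint is cut short, not lost.** Long-term means beyond 3 months, and 55 to 60 patients would have 6-month data. This also stands: the loss is modest at 12 months and severe only towards 24.
- **Late toxicity need not be underestimated.** A reader might infer a general downward bias. The Toxicity assessment section summarises clinician-reported toxicity as a proportion at each time point; among patients who have reached a visit, a smaller denominator costs precision and does not by itself bias the result. Bias arises only if a pooled incidence is divided by all 60, and the article fixes no such denominator. The same holds for withdrawal, where the 20% rate is my assumption.
- **A later report may exist.** A reader might infer that the 12- to 24-month data are never analysed. Early recruits do contribute such data at month 30, and the article condenses a fuller protocol, so a later report is plausible. But the article calls the month-30 analysis final and mentions no other, so the conflict in the text remains.
- **The 12-month shortfall depends on accrual.** It drops below a quarter if recruitment is strongly front-loaded, which the article does not plan. The 24-month shortfall exceeds half under every pattern tried.
- **The September 2026 date is minor.** Dates are given to the month and recruitment completion is an estimate; at most about 5 patients are affected under the assumed lag.

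**Conclusion.** The point holds as a stated rule that conflicts with the article's own schedule. It is not a detail left to an unseen analysis plan. That the final analysis comes before late recruits' 12- to 24-month assessments needs no assumption beyond the planned dates; the counts rest on uniform accrual and an assumed lag of 0 to 2 months. On that basis about three quarters or more of 24-month assessments, and a quarter to a third of 12-month assessments including the 1-year MRI, would be missing. The sample size rationale of 30 per arm is then not met at the late time points. The consequence is truncation and imprecision, with downward bias only for crude cumulative proportions of late toxicity or withdrawal that ignore unequal follow-up. The documents do not support the stronger conclusions that long-term toxicity is unassessable or that every late-toxicity figure would be too low.

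**What to change.** Reconcile Statistical analysis with Study setting, PROMs assessment, Table 1, Secondary outcomes and Exploratory outcomes:

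1. Keep the recruitment analysis at the end of the 24-month recruitment period.
2. Place the final analysis of toxicity, PROM, MRI and withdrawal data after the last participant's 24-month visit, and set the study completion date to cover that visit.
3. If an earlier look is wanted, label it preliminary and time it around 6 months after the last participant completes treatment, so that the 6-month assessments are complete.
4. Report cumulative late toxicity and withdrawal by a method that accounts for unequal follow-up, and give the number who have reached each visit beside every by-visit proportion.

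The cost is a change of wording and a final data lock about 18 months later (month 48 instead of month 30), plus any treatment lag for the last participant. No visits are added, and the primary feasibility result is not delayed.

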#### Future work

Demonstrating feasibility will facilitate a larger randomised study comparing salvage reirradiation options with ADT alone, the usual management option. This study would have primary endpoints of survival (overall and metastasis free). This is the first time that a hypoxia gene expression signature will be studied with hypoxia imaging in a prospective cohort of patients with radiorecurrent prostate cancer and could lead to the further studies investigating the introduction in clinical practice of tumour hypoxia testing (from biopsy and/or imaging) and the biological individualisation of radiotherapy. Given the large number of patients with prostate cancer who undergo radiotherapy each year, this would have a significant impact on personalised medicine in the UK.

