**Methods and analysis:**

The primary endpoint of the RO-PIP feasibility study is to evaluate the patient recruitment potential over 2 years to a trial randomising to either SBRT or HDR-BT for patients who develop local recurrence of prostate cancer following previous radiation therapy. The aim is to recruit 60 patients across 3 sites over 2 years and randomise 1:1 to SBRT or HDR-BT. Secondary objectives include recording clinician and patient-reported outcome measures to evaluate treatment-related toxicity. In addition, the study aims to identify potential imaging, genomic and proteomic biomarkers that are predictive of toxicity and outcome based on hypoxia status, a prognostic marker of prostate cancer.

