Prostate BT involves the placement of sealed radiation sources into the prostate and offers the ability to deliver highly conformal high-dose radiation with a steep dose gradient and rapid fall off in dose, which minimises radiation toxicity to surrounding organs at risk, specifically the rectum and bladder.^15^ Advances in image-guided-targeted BT may allow for more precise and focused treatments.^16–18^ BT can be delivered either via a permanent low-dose rate seed implant (LDR-BT), or via high-dose-rate BT (HDR-BT), which uses a high-activity radiation source (eg, iridium-192) that is temporarily introduced into applicators that are placed within the prostate, typically over 1–3 fractions. HDR-BT is less susceptible to issues related to prostate oedema and seed migration that might complicate dosimetry following LDR-BT. Current evidence suggests that HDR-BT affords lower toxicity, increased tolerability with similar oncological control compared with LDR-BT.^19^

Previously, salvage EBRT techniques have been associated with higher rates of severe late toxicities and also poor local control.^20^ Stereotactic body radiotherapy (SBRT), involving the delivery of a high dose of radiation to a highly conformal target volume with a steep dose gradient in a small number of fractions, may have benefits. Potential advantages include increased sparing of normal tissues than other types of EBRT and being less invasive compared with BT.^21^ BT is also highly specialised and only available in specialist centres.

A prospective trial is required to describe the toxicity profiles for these two most promising options, HDR-BT and SBRT, to allow clinicians and patients to make an informed decision on the most appropriate salvage treatment choice and help inform a larger study with an efficacy endpoint. Strategies to personalise salvage treatment through finding predictive genomic and imaging biomarkers are also required to optimise treatment outcomes.

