The reirradiation options for previously irradiated prostate cancer (RO-PIP) trial is the first prospective randomised trial to determine the feasibility of recruitment to a trial comparing SBRT and HDR-BT for locally recurrent prostate cancer and inform power calculations for a definitive randomised control trial (RCT). In addition, this feasibility trial will also quantify the impact on patient-reported outcome measures (PROMs), quantify longitudinal functional MRI changes and assess proteomic, immune and genomic biomarkers.

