### Assignment of interventions

Following confirmation of written consent and eligibility, participants will be randomised into the trial by the Leeds Clinical Trials Research Unit (CTRU). Patients will be randomised on a 1:1 basis to receive either HDR-BT or SBRT. Patients will be randomised using stratified permuted blocks, stratified by recruiting site and previous androgen deprivation therapy (ADT) therapy. Randomisation will be performed centrally using the CTRU 9–5 telephone randomisation system. Authorisation codes and personal identification numbers, provided by the CTRU, will be required to access the randomisation system.

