#### Additional interventions

ADT may be initiated at the discretion of the treating oncologist but this must be started by the time of the first salvage radiotherapy treatment (at first fraction of SBRT or at HDR-BT).

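### Meeting two randomisations per month would show recruitment to SBRT versus HDR-BT only, while the one larger trial described compares reirradiation with ADT alone on survival, for which no outcome is listed

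*Protocol article*

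**What the plan says.** **What is tested.** The abstract describes the primary endpoint as recruitment potential to a "trial randomising to either SBRT or HDR-BT for patients who develop local recurrence of prostate cancer following previous radiation therapy". Assignment of interventions confirms it: "Patients will be randomised on a 1:1 basis to receive either HDR-BT or SBRT". There is no ADT-alone arm. ADT enters only as an optional addition in either arm: "ADT may be initiated at the discretion of the treating oncologist" (Additional interventions).

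**What the result is for.** The Primary outcome section gives the purpose of the recruitment criterion: "To show that patient recruitment targets for a phase III RCT can be met within an adequate timeframe". The criterion is an average of two patients randomised per month. The Introduction adds that the trial will "inform power calculations for a definitive randomised control trial (RCT") and will "help inform a larger study with an efficacy endpoint". The Sample size section says that recruitment and toxicity rates together will decide whether a larger RCT is feasible.

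**The larger trial described.** Future work is the only place that sets out a larger trial's comparison and primary endpoints: "Demonstrating feasibility will facilitate a larger randomised study comparing salvage reirradiation options with ADT alone, the usual management option", and "This study would have primary endpoints of survival (overall and metastasis free").

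**What is measured.** The listed outcomes are recruitment (primary); patient-reported and CTCAE toxicity, quality of life and process measures (secondary); and MRI, hypoxia and cytokine biomarkers with image quality (exploratory). Table 1 also schedules PSA at six time points, and clinical history and outcome data at baseline and 24 months. No listed outcome uses either.

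**The concern.** Agreeing to be allocated between two forms of salvage radiation is a different decision from agreeing to possible allocation to no local salvage at all. Equipoise among clinicians differs too: the Introduction cites a registry in which only 15%–20% of men with local recurrence after radiotherapy have local salvage, and Future work calls ADT alone the usual management. The recruitment rate against ADT alone could be lower or higher than the rate observed here; this trial cannot say which.

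Two things are at stake. First, a result at or above two per month could be carried into a phase III funding or go-ahead decision for a comparison whose recruitment was never tested. Second, a trial with survival endpoints is sized on event rates, and this trial as listed would end without reporting one, even for the reirradiation arm.

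**Working it through.** **1. The plan's own recruitment figures.** 60 patients / 24 months = 2.5 per month, which agrees with the stated 2–3 per month. The criterion of two per month gives 2 × 24 = 48 patients. Both figures count men randomised between SBRT and HDR-BT. The number offered randomisation against ADT alone is 0 by design.

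**2. Aim against evidence.**

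| Needed for the trial in Future work | Supplied here? |
|---|---|
| Recruitment rate, reirradiation versus ADT alone | No; a different randomisation is offered |
| Event rate under ADT alone | No; there is no such arm |
| Event rate under reirradiation | Not among the listed outcomes |
| Toxicity, compliance, withdrawal under reirradiation | Yes |

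**3. Why the event rate matters.** Illustration only: the documents give no hazard ratio, alpha or power for the later trial, so these are assumed. With two-sided alpha 0.05 and 1:1 allocation, the Schoenfeld formula is events = 4(z₁₋α/₂ + z₁₋β)² / (ln HR)².
- HR 0.6, 80% power: 121 events
- HR 0.7, 80% power: 247 events
- HR 0.75, 80% power: 380 events
- HR 0.8, 90% power: 845 events

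Patients = events / (proportion having an event), so event rates in both arms are needed to turn any of these into a sample size. Toxicity rates do not provide them.

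**4. What the scheduled data could provide.** Table 1 marks PSA at baseline and at 3, 6, 12, 18 and 24 months. At full recruitment and before attrition, that is 5 × 60 = 300 follow-up values plus 60 baseline values.

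Follow-up at the planned analysis is limited. Statistical analysis places the final analysis 6 months after the last randomisation, which is month 30 if recruitment takes the full 24 months. Assuming even accrual:
- 24 months from randomisation is reached by those randomised by month 6: 6/24 × 60 = 15 men.
- 12 months is reached by those randomised by month 18: 18/24 × 60 = 45 men.

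Visits are timed from the end of treatment, so the true numbers are somewhat lower. Kaplan-Meier handles this censoring, but the 24-month end of the curve would rest on few men.

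Precision with both arms pooled and complete follow-up (a best case) is a 95% half-width of 1.96 × √(p(1−p)/60). For assumed p = 0.1, 0.2 and 0.5 this gives about 7.6, 10.1 and 12.7 percentage points.

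**5. What they could not provide.** The only scan in Table 1 is prostate mpMRI, at baseline, 1 month and 12 months. No staging imaging is scheduled, so metastasis-free survival is not systematically ascertained.

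**The case against.** The strongest reply is that the documents never join these statements. Primary outcome speaks only of a phase III RCT, and the Introduction only of a definitive one; neither names ADT alone. In the Introduction the power-calculation aim directly follows the SBRT versus HDR-BT comparison, so a definitive trial of that comparison is a natural reading. Future work says that feasibility will facilitate the ADT-alone trial, not that it decides it. The plural in its reirradiation options may mean a multi-arm trial that keeps both techniques. A feasibility trial need not be powered for efficacy, and the article says this one is not.

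Much of this stands. A reader might infer that the two-per-month criterion was set for the ADT-alone trial, or that passing it unlocks that trial. The text supports neither. Nor does it support a complaint about lack of power, or a claim that nothing here helps later planning: recruitment, toxicity, compliance, withdrawal and reasons for non-recruitment all do.

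The mismatch remains. In a multi-arm trial, the evidence would carry over to the SBRT/HDR-BT part but not to randomisation against ADT alone. If instead the definitive trial is SBRT versus HDR-BT, the article describes no such trial in Future work, and the Introduction still expects a later efficacy endpoint with no efficacy outcome listed here.

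It is also fair to say that the full protocol or SAP may describe how PSA is summarised. That weakens the outcome part of the point, but no analysis plan can change which randomisation was offered.

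Finally, added survival outcomes would be modest in value. Entrants are non-metastatic with more than 10 years' life expectancy, so few deaths are likely. Discretionary ADT, with testosterone scheduled only at baseline, complicates PSA-based failure. All of this stands and limits the fix.

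**Conclusion.** The point holds as one about what may be concluded. Recruitment at two per month or above would support recruitment to randomisation between SBRT and HDR-BT. It would not support recruitment to randomisation against ADT alone, which 0 participants are offered. The listed outcomes include no tumour-control or survival measure, so the aim of informing power calculations is met for recruitment, compliance, withdrawal and toxicity, but not for the survival endpoints named in Future work. Even with the outcomes added, the event rate under ADT alone must come from elsewhere.

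The validity of the trial for its own feasibility question is not affected. The conclusion rests on the arms, outcome lists and schedule as printed in the article. It does not depend on the assumed hazard ratios or on even accrual, which only illustrate scale.

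**What to change.** **1. Wording.** State in Primary outcome and in Future work that meeting the criterion supports recruitment only to randomisation between SBRT and HDR-BT, not to randomisation against ADT alone; or reconcile the future trial with the comparison tested. In the Introduction, limit the power-calculation aim to the parameters this trial can estimate. Cost: a narrower feasibility claim.

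**2. Outcomes.** Add biochemical failure-free survival and overall survival as descriptive secondary outcomes. Fix the definition of biochemical failure in advance. Report Kaplan-Meier estimates with 95% confidence intervals, censored at the analysis date and not compared between arms, with biochemical results also shown by ADT use. Report metastases only as captured in the 24-month outcome data. Cost: a short table from follow-up already scheduled. The estimates will be imprecise, will inform the reirradiation arm only, and will be incomplete to 24 months unless Statistical analysis adds a later analysis. The study completion date of September 2026, 24 months after recruitment is due to close, leaves some room for one.

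**Optional.** A screening-log question on whether eligible men, including decliners, would accept randomisation against ADT alone would give indirect evidence. Stated willingness is not recruitment, however, and putting the question to decliners may need consent and ethics review. It is not part of the core change.
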